### Measures

All participants will be contacted by telephone to schedule the **inclusion visit (visit 1)**, which will include the standardized medical tests and completion of a data collection questionnaire containing the following information:Sociodemographic and family data: age, sex, ethnicity, marital status, number of children, education level, socioeconomic status, employmentHistory of diseases and respiratory symptomsTobacco use: current number of cigarettes/day), cumulative consumption (packs/year) and age when the participant started smokingDietary habits and lifestyleAlcohol use, measured in units/week (one unit = 10 gr alcohol)Food Frequency Questionnaire [20]Questionnaire on MD Adherence (14 points) [21]Minnesota Leisure Time Physical Activity Questionnaire, validated for the population of Spain [22]Basic physical examination, including weight (Kg), height (cm), body mass index (BMI = Kg/m^2^), waist circumference (cm) and blood pressure (mmHg)Exhaled carbon monoxide measured by carboximetry12-lead electrocardiogramBasic blood tests to measure glucose, triglycerides, cholesterol (total, high-density lipoprotein and low-density lipoprotein, creatinine and transaminases (aspartate-aminotransferase and alanine-aminotransferase).Forced spirometry and bronchodilation test to obtain FVC and FEV_1_ values and the FEV_1_/FVC% ratio, following current guidelines [23].

The primary outcome variable to determine whether the objective has been met will be the change in lung function indicated by spirometry, FVC, FEV_1_ and FEV_1_/FVC %. The secondary outcomes variables will be changes in MD pattern, anthropometric measurements (weight, BMI and waist circumference) and smoking habit.

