### Statistical analysis

The study will use an intention-to-treat analysis and the main outcome variable will be measured at the beginning of the study for each participant. The effectiveness of the simple randomization will be evaluated by the comparability and homogeneity of the two groups in terms of the baseline distribution of the study variables. Losses to follow-up will be calculated for each group and evaluated to determine whether the proportion of losses is independent of assignment to the intervention or control group.

Qualitative variables will be described as frequencies or percentages and quantitative variables by means and standard deviations if they follow a normal distribution, or median and interquartile range.

Variables will be stratified by study group; basal comparison will be done by x^2^ test for qualitative variables and Student t or Mann–Whitney U for quantitative variables. Data from the initial MD Adherence Questionnaire and Food Frequency Questionnaire (V1) will be compared to the final questionnaire data (V5). In addition, changes from baseline in lung function after the corresponding nutritional intervention, will be compared for both groups. If important clinical differences are observed, multivariate analysis will be used to determine which factors are independently associated with the outcomes, adjusting for covariates such as age, sex, ethnic group, height, BMI, education level, smoking habit, physical activity or total caloric intake [6]. The results will be presented using relative measures including relative risk (RR) and relative risk reduction (RRR), and absolute risk reduction (ARR), with 95% confidence intervals. All analysis will be done with SPSS version 22.0, considering differences to be significant when *p* < 0.05.

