The theoretical framework is the provision of personalized and motivational information about the benefits of adopting a dietary pattern based on the MD. Recent studies have shown that one of the major aspects of this model of healthy eating is that is based on diet quality more than on the relative quantities of specific nutrients consumed [30]. Therefore, the program focuses on two major areas of emphasis: 1) reinforcement of the consumption of foods belonging to the traditional MD pattern (also known as a *prudent* diet) and considered protective because of their nutritional composition, including virgin olive oil, nuts, legumes/pulses, salads, fruits and vegetables, whole grains, fibre-rich foods, and fish, and 2) decrease consumption of foods whose nutritional composition has negative effects (also known as a *Western* diet), such as fast food, commercially prepared foods, sausages or processed meats and patés, refined sugars and flours, sugary drinks, French fries, transfats (e.g., commercial pastries), sweets and desserts [31]. Each participant in the intervention group will receive guidance based on his or her scores from the 14-point MD Adherence Questionnaire and Food Frequency Questionnaire. The annual administration of these instruments, validated for the population of Spain and used in other prospective studies [16], will allow us to evaluate the level of MD adherence as well as changes during follow-up, ensuring a high-quality measurement of a participant’s actual diet. Nevertheless, a potential study limitation in the subjective nature of the information obtained. A possible line of future research will be the measurement of biomarkers of the MD pattern such as the level of oleic and alpha- linoleic acids, reliable indicators of an individual’s intake of monounsaturated and polyunsaturated fatty acids, respectively, and urinary concentrations of tyrosol and hydroxityrosol (olive oil) and resveratrol and ethanol (wine and alcoholic drinks in general).

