With the goal of minimizing the possible losses to follow-up, a common concern in long-term projects, and increase the motivation of study participants, a multicomponent intervention has been designed. The use of new technologies has proven useful in health care settings, reducing costs and improving treatment adherence [32]. The creation of the DIET Blog as a nutritional tool 2.0 to reinforce the nutritional education program is intended to increase MD adherence during follow-up. In addition to making recipes and educational materials available periodically, the blog will provide an ongoing “reminder” of the benefits of a balanced diet and facilitate a more agile and flexible interaction between participants in the intervention group and the dietician, beyond their consults in the primary care centre.

With respect to group sessions, the third component of the intervention design, these will be more recreational. In addition to reinforcement of the main items that are characteristic of the MD pattern and the opportunity to clear up any questions or misunderstandings, the sessions will encourage participants to exchange experiences, raise awareness and increase motivation. This will affect the change in attitudes that is absolutely necessary to initiate changes toward eating habits that are healthy and balanced, along with other lifestyle habits such as physical exercise, smoking cessation, etc.

Knowledge and skills are essential to properly evaluate MD adherence in terms of specific foods, as well as to increase the validity and reliability of the information collected using the study questionnaires. Therefore, the expertise of an experienced, highly qualified nutritionist is a fundamental requirement for the success of the nutritional intervention and participant follow-up.

The effect on lung function will be evaluated by comparing the results of three consecutive forced spirometry measurements, taken annually during the three-year project period. Although in theory this time period is sufficient to allow observations about the longitudinal effects of the diet on spirometry values, it could be too short to show statistically and clinically significant differences between the two groups. In any case, these results should provide additional evidence of the effect of a Mediterranean-type dietary pattern on lung function in a population of smokers with no previous respiratory disease.

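### The adjusted analysis is triggered by undefined observed differences and draws on an open covariate list that is not limited to visit 1 values and leaves out baseline lung function

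*Protocol article*

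**What the plan says.** Three parts of the protocol article bear on this.

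- **Statistical analysis, the between-group comparison.** After an intention-to-treat statement and tests of baseline comparability, the section says that "changes from baseline in lung function after the corresponding nutritional intervention, will be compared for both groups". No trigger and no covariates are attached.
- **Statistical analysis, the adjusted model.** The next sentence reads "If important clinical differences are observed, multivariate analysis will be used to determine which factors are independently associated with the outcomes", and continues "adjusting for covariates such as age, sex, ethnic group, height, BMI, education level, smoking habit, physical activity or total caloric intake". No threshold is given, and it is not said whether the differences are in outcomes or at baseline. The list is open-ended, gives no measurement time, and does not contain the baseline value of the spirometric outcome.
- **Measures and Discussion.** Two of the listed covariates are also outcomes: "The secondary outcomes variables will be changes in MD pattern, anthropometric measurements (weight, BMI and waist circumference) and smoking habit". The Discussion expects the group sessions to help change eating habits "along with other lifestyle habits such as physical exercise, smoking cessation, etc".

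**The concern.** Two separate problems follow from the wording.

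First, the data decide whether an adjusted result exists. If the trigger is a difference in lung function, the adjusted estimate is produced only in trials where the observed effect happened to look large, so on average it overstates the truth. If the trigger is baseline imbalance, adjustment depends on tests between groups that were formed by randomisation. Those tests say little about which covariates are worth adjusting for.

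Second, BMI, smoking habit and physical activity may change after randomisation, and may change differently in the two groups. Adjusting for their follow-up values no longer estimates the total effect of assignment, because any part of the effect carried by them is taken out. Adjusting for their visit 1 values does no such harm and may add precision. The text does not say which is meant.

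At stake is an adjusted result that readers would naturally set beside the unadjusted one. The section does not say which governs if they disagree.

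**Working it through.** **The plan's own figure.** The plan gives no number for this point. The nearest is the 40 per group in the Sample size section (two-sided 5%, 80% power). No SD is stated, so 40 can only be solved backwards. The standardised difference detectable with 40 per group is (1.960 + 0.842)/√(40/2) = 2.802/4.472 = 0.626 SD. For the stated 10-12 ml/year this implies an SD of 10/0.626 = 16.0 to 12/0.626 = 19.2 ml/year. The point does not depend on that SD; 0.626 is used below only as a reasonable effect size.

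**Which covariates could carry treatment effect, on the article's own words.**

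| Covariate | What the article says | Could change with treatment? |
|---|---|---|
| Age, sex, ethnic group, height, education | Collected at visit 1 | No material route |
| BMI | Change is a secondary outcome | Yes |
| Smoking habit | Change is a secondary outcome; cessation mentioned for the sessions | Yes |
| Physical activity | Exercise mentioned for the sessions | Yes |
| Total caloric intake | No calorie aim stated | By inference only |

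Both timings are available. The Measures section puts the instruments in the visit 1 battery, and the Intervention section says the annual follow-up visits repeat visit 1. All participants smoke at entry, so smoking status itself cannot vary at visit 1; only intensity or cumulative exposure can. A smoking covariate coded as status would therefore have to be a follow-up value.

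**Effect of the timing.** Suppose treatment shifts the covariate by *a* and each unit of the covariate shifts the outcome by *b*. The part carried by the covariate is *a* × *b*, and follow-up adjustment leaves total − *a* × *b*. This was simulated with 40 per arm, linear regression and 5,000 runs. The assumptions, none from the documents, were: total effect 0.626 SD, *a* = 0.5 SD, baseline-to-follow-up correlation of the covariate 0.7, and *b* = share × 0.626/0.5.

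| Assumed share through covariate | Expected after follow-up adjustment | Simulated: follow-up value | Simulated: visit 1 value | Power: unadjusted / visit 1 / follow-up |
|---|---|---|---|---|
| 0% | 0.626 | 0.620 | 0.620 | 0.78 / 0.78 / 0.75 |
| 25% | 0.470 | 0.473 | 0.629 | 0.80 / 0.81 / 0.57 |
| 50% | 0.313 | 0.312 | 0.625 | 0.79 / 0.86 / 0.40 |
| 75% | 0.157 | 0.156 | 0.628 | 0.79 / 0.95 / 0.50 |

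Follow-up adjustment removes exactly the share that was assumed; visit 1 adjustment removes none. The shares are inputs, not estimates. The 75% row needs *b* = 0.939, meaning the covariate explains *b*² = 88% of the within-group outcome variance, and serves only as an extreme.

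**Effect of the trigger.** Take the outcome reading, and represent an important difference by a significant unadjusted benefit (an assumption, since the plan defines nothing). The mean visit 1-adjusted estimate among triggered trials was 0.705, 0.703, 0.690 and 0.674 SD in the four rows, against a true 0.626. The overstatement runs from 0.674/0.626 − 1 = 8% to 0.705/0.626 − 1 = 13%. Run in every trial, the same model averaged 0.62-0.63.

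**Baseline lung function.** For outcomes with equal variance σ² at both visits and correlation ρ, a change score has variance 2(1 − ρ)σ², and adjustment for the baseline value leaves (1 − ρ²)σ². The ratio of the second to the first is (1 + ρ)/2, which never exceeds 1. Adding the visit 1 value therefore cannot lose precision relative to the change score, apart from one degree of freedom. The gain is small if ρ is close to 1; the documents give no ρ.

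**The case against.** The strongest reply is that the randomised comparison is already protected. The change in lung function is compared between groups unconditionally and unadjusted, and the multivariate model is a follow-on with a different stated purpose. That stands. A reader might infer that the trial's main estimate is conditional or biased by these covariates; the text does not support this.

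The second reply is that nothing says follow-up values will be used. The list mixes fixed traits with variables all measured at visit 1, and a condensed article may leave timing to an analysis plan that is not shown. That also stands in part: unstated timing alone would not be a finding. But the article does more than omit detail. It fixes a trigger and names covariates that are its own outcomes, and that rule needs changing wherever the timing is settled.

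Third, a reader might infer that the programme is meant to change total calories. The Discussion says the dietary model "is based on diet quality more than on the relative quantities of specific nutrients consumed" and sets no calorie target. One aim is to "decrease consumption of foods whose nutritional composition has negative effects", which could lower intake, but that is an inference.

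Fourth, a reader might infer an inflated type I error from having two results to choose between. That needs a rule of reporting whichever is significant, and the protocol states none.

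Finally, baseline lung function is not ignored, because the outcome is a change. Its absence from the adjusted model is a missed improvement rather than an error.

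**Conclusion.** The point holds for the adjusted model only. Its trigger is undefined and data-dependent on either reading, its stated purpose is not the effect of assignment, and its covariate list leaves post-randomisation values of BMI, smoking habit and physical activity open.

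On size: selection on an observed significant benefit overstated the adjusted estimate by about 8-13% in the illustrative simulation, given a true effect of 0.626 SD and 40 per arm. The loss from follow-up adjustment equals the share of effect carried by the covariates. That share could be nil or large, and nothing in the documents allows it to be derived. It is tempting to say that adjustment will remove part of the effect; this is true only if follow-up values are entered and they carry effect.

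This is worth correcting before the data are analysed, because it costs nothing and protects the one adjusted result the trial will report. It does not undermine the unconditional comparison, so it is not among the most serious class of defects.

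**What to change.** Revise the Statistical analysis section as follows.

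- Delete the condition on observed differences, and do not let baseline significance tests decide adjustment.
- Pre-specify one adjusted between-group model for each lung-function outcome, run whatever is observed: the visit 5 value (or the change) on randomised group, adjusted for the visit 1 value of that outcome and a short list of visit 1 covariates, for example age, sex, height and cigarettes per day. With the visit 1 value in a linear model, the visit 5 value and the change give the same group coefficient, so that choice is immaterial.
- State that the purpose is to estimate the effect of assignment, and say how this result stands in relation to the unadjusted comparison.
- Label any model using follow-up smoking, BMI, physical activity or caloric intake as exploratory.

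The cost is analysis wording only; the suggested variables are already collected at visit 1. The change leaves open which of the three lung-function outcomes takes precedence, which is a separate question.

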### Sample size/power calculation

A sample of 40 participants in each group will be required to observe significant differences in lung function between groups (decrease in FEV_1_ > 10–12 ml/year), in a two-tailed test with a mean FEV_1_ value of 95%, significance level of 5%, 80% strength and less than 15% losses to follow-up [24].

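### The protocol names risk measures (RR, RRR, ARR) for its results, but the primary outcome is a continuous change with no event defined, and no mean difference is named

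*Protocol article*

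**What the plan says.** Four statements in the protocol article bear on this.

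- **Measures** defines the primary outcome: it "will be the change in lung function indicated by spirometry, FVC, FEV_1_ and FEV_1_/FVC" %. The secondary outcomes listed there are changes in MD pattern, in weight, BMI and waist circumference, and in smoking habit.
- **Sample size/power calculation** sizes the trial to detect "significant differences in lung function between groups (decrease in FEV_1_ > 10–12 ml/year"), with 40 per group.
- **Statistical analysis** plans the comparison on the same scale: "changes from baseline in lung function after the corresponding nutritional intervention, will be compared for both groups".
- **Statistical analysis**, near its end, then fixes how findings are expressed: "The results will be presented using relative measures including relative risk (RR) and relative risk reduction (RRR), and absolute risk reduction (ARR"). Each is to carry a 95% CI.

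The last statement is not confined to any outcome. The Intervention section adds that the 14-item MD questionnaire sorts participants into three adherence bands. No section names an event, responder or threshold for lung function.

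**The concern.** RR, RRR and ARR are functions of two proportions, so they need a yes/no event for each participant. Change in FVC, FEV1 or FEV1/FVC gives a mean and a spread, not a proportion. The same holds for weight, BMI, waist and the numeric MD score. As worded, the only effect measures that the document commits to cannot be produced for the outcome on which the trial is to be judged. The measure that does fit, a difference in mean change, is not mentioned.

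Two things are at stake. First, the reported estimate and interval would not correspond to the planned comparison or to the ml/year difference that set the sample size. Second, an analyst who follows the sentence literally would have to create an event. That discards information in a small trial and leaves a threshold to be chosen for each of three spirometry parameters, possibly after the data are seen.

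**Working it through.** **1. Match of measure to outcome**

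| Outcome | Scale | Event defined? | RR/RRR/ARR calculable as written? |
|---|---|---|---|
| Change in FVC, FEV1, FEV1/FVC (primary) | continuous | no | no |
| Weight, BMI, waist | continuous | no | no |
| MD score (14 items) | numeric | bands exist, no event chosen | only once a band is chosen |
| Smoking habit | can be made binary | not spelled out | yes, once defined |

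The figure of 10–12 ml/year in the sample-size section cannot serve as the missing event. It is a range, and it is worded as a difference between groups, not as a threshold for an individual.

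**2. The plan's own figure**

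Inputs from the sample-size section: 40 per group, two-tailed 5%, 80% power, difference 10–12 ml/year. No SD is given, so 40 cannot be reproduced directly. It can only be solved backwards.

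- Standardised effect = (1.960 + 0.842) × √(2/40) = 2.802 × 0.2236 = 0.626.
- Implied SD of annual change = 10/0.626 ≈ 16.0 ml/year, or 12/0.626 ≈ 19.2 ml/year.
- If 40 already allows for 15% losses, 40 × 0.85 = 34 are evaluable. The effect is then 0.679 and the SD about 14.7 or 17.7 ml/year.

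The 80% used below is therefore nominal: it is what the document claims, not something that its inputs establish.

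**3. What dichotomising would cost, if it were done**

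Assumptions: normal outcome, equal SDs, 40 evaluable per group, effect 0.626. The cut-points are illustrative, since the document gives none.

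For a split at the pooled median, the two proportions are Φ(0.626/2) = 0.623 and 0.377, a difference of 0.246.

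- SE under no difference = √(2 × 0.5 × 0.5/40) = 0.1118.
- SE under the alternative = √(2 × 0.623 × 0.377/40) = 0.1084.
- Power = Φ[(0.246 − 1.960 × 0.1118)/0.1084] ≈ Φ(0.25) ≈ 0.60.
- Number needed for 80% power: 64 per group.

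For a cut that gives a chosen event rate in controls, the intervention rate is 1 − Φ(c + 0.626), where c is the normal quantile for the control rate:

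| Event in controls | Event in intervention | Power, 40 per group | Per group for 80% |
|---|---|---|---|
| 20% | 7.1% | 39% | 110 |
| 30% | 12.5% | 48% | 85 |
| 50% | 26.6% | 58% | 67 |
| 70% | 45.9% | 59% | 65 |
| 80% | 58.5% | 55% | 72 |

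Cross-check: starting from the t-test effect for 80% power (0.634), a fixed mid-point split gives 63% by exact enumeration of the two-proportion z-test, and simulation agrees. The large-sample efficiency of a median split is 2/π = 0.637, so 80 participants would carry the information of about 80 × 0.637 = 51.

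With 34 evaluable per group (effect 0.679), power over the same cuts is about 38–60%, and 55–97 evaluable per group would be needed.

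**The case against.** The strongest reply is that the same section already plans to compare changes from baseline in lung function between groups, and describes quantitative variables by means and SDs or by medians and interquartile ranges. The sentence on risk measures concerns presentation. Its list is introduced as non-exhaustive, and it could have been written with smoking habit or MD adherence bands in mind. On that reading lung function is analysed as continuous, no power is lost, and the sample-size basis is intact. Cut-points and outcome-by-outcome detail are also commonly left to a SAP or full protocol.

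Much of this stands. A reader might infer that the trial is bound to dichotomise its primary outcome, that its power therefore drops to about 63%, or that the link to the sample size is broken. The document supports none of these, because the planned comparison of changes remains.

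The mismatch itself is not answered. The sentence covers the results in general and is not limited to categorical outcomes. The outcomes it might suit are secondary. Even on the generous reading, the primary outcome is left without a named effect measure. Nor is this a detail deferred to a SAP: the article positively states measures, and they are of the wrong type for its own primary outcome.

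**Conclusion.** The point holds as a mismatch between stated effect measures and outcome. RR, RRR and ARR cannot be calculated for change in FVC, FEV1 or FEV1/FVC as the document defines them. They do not correspond to the planned comparison of changes or to the ml/year difference used for the sample size. This conclusion rests on the text alone and needs no numerical assumption.

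The power loss is conditional. It arises only if lung function is dichotomised to obtain the risk measures in place of the continuous comparison. In that case nominal 80% power falls to about 60–63% for a median or mid-point split and to about 39% for the most extreme cut examined. These figures assume normality, equal SDs, all 80 participants evaluable and a starting power taken from the document's claim. The direction is robust; the size depends on the cut-point. If lung function stays continuous, the loss is nil and the defect is one of reporting.

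**What to change.** Replace the sentence on risk measures with two statements:

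- FEV1, FVC, FEV1/FVC, MD score, weight, BMI and waist circumference are reported as the between-group difference in mean change, in their own units (ml or ml/year, percentage points, points, kg, kg/m², cm), with 95% CI.
- RR, RRR and ARR with 95% CI are used only for binary outcomes defined in advance, such as smoking status at V5 or reaching a pre-specified MD adherence category.

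If a lung-function responder analysis is wanted as well, its threshold should be fixed before the outcome data are seen and the analysis labelled supportive.

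The cost is a short edit to the analysis section, with no extra participants, visits or measurements. It should be made before outcome data are examined.
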